### Primary outcomes

#### Quality of life

Quality of life will be measured subjectively using the Quality of Life Questionnaire-Core (QLQ-C30), which as a core questionnaire has been used in a wide range of cancer clinical trials [11]. It is supplemented by disease specific modules. Categories include functional scales, global health status and QOL scale, in addition to several single-item symptom measures [12, 13]. In the current study, QLQ-C30 will be collected via online app with patients at baseline, week 2, 4 and 6 during intervention or usual care phase (Table 3).

**Table 3 Tab3:** Study assessment procedures and timetable

Visit schedule	pre	Treatment phase			Follow-up phase		
Study phase	Baseline testing	T1	T2	T3	T4	T5	T6
Week/year	Baseline	Week 2	Week 4	Week 6	1 year	2 years	3 years
**General data**							
Eligibility screening	√						
Informed consent	√						
Baseline information	√						
IPAQ scale	√						
**Efficacy parameters**							
SAS	√	√	√	√			
SDS	√	√	√	√			
FCRI	√	√	√	√			
QLQ-C30	√	√	√	√			
TCM-SS	√	√	√	√			
TCM-SDS/TCM-KDS	√	√	√	√			
CaSUN	√	√	√	√	√	√	√
Caner recurrence/other outcome events					√	√	√
**Safety parameters**							
Adverse events		√	√	√			
End of treatment				√			

#### Self-reported psychological stress

##### The Self-Rating Anxiety Scale (SAS)

The scale includes 20 items and have four grades (Grade I-IV), ranging from I, which considers anxiety from normal, to Grade IV, which describes the most severe anxiety of the patients [14].

##### The Self-Rating Depression Scale (SDS)

To assess the severity of depressive symptoms, the self-rating depression scale is used. The scale consists of 20 items [15, 16], measuring the severity of depressive symptoms on a four-point Likert scale.

##### Fear of Cancer Recurrence Inventory (FCRI)

We use the fear of cancer recurrence inventory (FCRI) to evaluate the participants’ fear of recurrence (FCR). FCRI is a 42-item scale which is recognized as one of the psychometrically strongest measures of FCR [17–19]. Higher scores indicate a greater level of psychological distress.

### Secondary outcomes

As secondary outcomes, The Cancer Unmet Needs (CaSun), Traditional Chinese Medicine syndrome scale (TCM-SS) and TCM spleen deficiency scale (TCM-SDS) will be applied. Another secondary efficacy endpoint of the study is Disease Free Survival (DFS), defined as the time from the date of randomization up to the date of first local, regional, or distant relapse. The follow-up will begin when the patient completes treatment phase. The follow-up visits will be done every year lasting for 3 years. Patients will do abdominal US (ultrasound) and CT (Computerized Tomography) and conduct the information including lifestyle, psychological state, and social relations.

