**Methods:**

We design a phase II RCT study, in which 210 CRC patients who have received radical surgery (stage I-III) will be recruited. Eligible patients will be randomly assigned to TCM-eRhab group or usual care group by 2:1 ratio. Patients in the intervention group will receive the structured TCM-eRhab program for six weeks, while patients in control group will receive usual care only. The primary outcomes are quality of life, severity of anxiety, depression and fear of cancer recurrence. Cancer recurrence rate will also be calculated according to long term follow-up data.

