### Statistical analysis

Analysis of the study will be performed using SPSS statistical software package, version SPSS26.0 (Chicago, IL, USA) by the “intention-to-treat” principle, therefor all randomized patients satisfying eligibility criteria will be included in the efficacy analysis. A comparison of demographic, social and clinical characteristics will be carried out for each arm. The primary analysis of the QLQ-C30 questionnaire and Self-reported psychological pressure scales is the domain-averaged difference in scores between TCM-eRhab intervention group and usual follow-up group after intervention. Difference in these variables between the intervention and control groups will examined using either chi-square tests or analysis of variance. To examine whether anxiety, depression and clinical syndromes are the prediction factors of metastasis after intervention, modelling will be performed in Stata.

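### The endpoint called Disease Free Survival counts relapse but not death, so as written it is time to recurrence under a survival name

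*Protocol article*

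**What the plan says.** Under Secondary outcomes, the Protocol article lists Disease Free Survival (DFS) as a secondary efficacy endpoint, "defined as the time from the date of randomization up to the date of first local, regional, or distant relapse". No other event is listed and nothing is said about death.

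The same section says "The follow-up will begin when the patient completes treatment phase" and "The follow-up visits will be done every year lasting for 3 years". In Table 3 the row "Caner recurrence/other outcome events" is ticked at years 1, 2 and 3 and not at weeks 2, 4 or 6. The term for other events is not defined. The row "Adverse events" is ticked only at weeks 2, 4 and 6.

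The long-term outcome is described differently elsewhere. The end of the Introduction plans to assess survival outcomes, DFS above all, and the Discussion places DFS within the study's main objective. The Abstract (Methods) says instead: "Cancer recurrence rate will also be calculated according to long term follow-up data". Statistical analysis states the intention-to-treat principle and says that "all randomized patients satisfying eligibility criteria will be included in the efficacy analysis".

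**The concern.** The name and the definition disagree. A disease-free survival time ends when the patient is no longer both alive and free of disease, so death has to end it. With a relapse-only event list, a patient who dies without relapse contributes no event.

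Three things follow. A result published as DFS would not be comparable with DFS that includes death. A difference between arms in deaths without relapse, in either direction, would not show in the endpoint. And a conclusion about survival would rest on a measure from which death is absent. The prominence given to DFS in the Introduction and Discussion makes this more than a labelling slip in a minor endpoint.

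The follow-up wording adds a smaller difficulty. The clock starts at randomisation, but the text starts follow-up at the end of the treatment phase, and no visit in the first six weeks is marked for relapse or other outcome events.

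**Working it through.** The document gives no DFS rate, event count, hazard ratio or power, so there is no figure of its own to reproduce. The check is a comparison of statements, followed by an illustration of scale.

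**Statements side by side**

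| Place in the Protocol article | Content |
|---|---|
| Secondary outcomes | Name: DFS. Origin: randomisation. Events: local, regional or distant relapse |
| Introduction; Discussion | DFS presented as a survival outcome |
| Abstract (Methods) | Recurrence rate |
| Table 3, efficacy rows | Recurrence and undefined other events, years 1 to 3 only |
| Table 3, safety rows | Adverse events, weeks 2, 4 and 6 only |

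The Abstract's wording fits the definition; the survival wording does not. The undefined other events in Table 3 may include death, but that would only mean that deaths are recorded. It does not make death a DFS event. No row of Table 3 names death, and the safety row stops at week 6.

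**Scale, for illustration only**

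Inputs: 210 patients (Sample size); 5-year survival of 60-80% for early-stage disease (Introduction); 3 years of follow-up (Secondary outcomes). Assumed, not in the document: a constant hazard, survival used as a stand-in for DFS, and 10-20% of first events being deaths without relapse.

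- Hazard per year = -ln(S5)/5. For S5 = 0.80 this is 0.0446; for S5 = 0.60 it is 0.1022.
- Probability of an event by year 3 = 1 - S5^(3/5). For 0.80: 1 - 0.875 = 0.125. For 0.60: 1 - 0.736 = 0.264.
- Events in 210 patients: 210 × 0.1253 = 26.3 and 210 × 0.2640 = 55.4, so about 26 to 55.
- Deaths without relapse left uncounted: 0.10 × 26.3 = 2.6 to 0.20 × 55.4 = 11.1, so about 3 to 11.

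A second set of assumed rates checks how far this depends on the proxy. With 10-30% relapsing within 3 years there would be 21 to 63 relapses. With 1-5% dying without relapse there would be 2.1 to 10.5 such deaths. The uncounted share of all relapse-or-death events then runs from 0.01/(0.30 + 0.01) = 3% to 0.05/(0.10 + 0.05) = 33%. The count is similar, but the share depends heavily on the assumptions.

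**Events in the first six weeks**

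Six weeks is 6/52.18 = 0.115 year. At the two proxy hazards, 210 × (1 - exp(-0.0446 × 0.115)) = 1.1 and 210 × (1 - exp(-0.1022 × 0.115)) = 2.5 events. Few events fall in the period with no scheduled collection point.

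**The case against.** DFS is a secondary endpoint, the sample size rests on the QLQ-C30 alone, and no power is claimed for DFS. An article may also leave the handling of deaths and censoring to an analysis plan that is not shown. This stands as far as it goes: nothing in the text says that deaths will be censored, and the analysis method for DFS is not at issue. But the event list is not left open. The article states it in full, and a rule for handling deaths elsewhere would not turn death into an event.

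A reader might go further and infer three stronger claims that the document does not support.

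- *Relapses in weeks 0 to 6 are lost.* The clock starts at randomisation and the first relapse counts, so an early relapse remains an event if it is found and dated later, at the year-1 visit or through the surveillance described under Usual care (Control) group. Only a scheduled collection point is missing.
- *Patients who do not complete treatment are excluded from DFS, more so in the intervention arm.* Table 3 divides the study into a treatment phase and a follow-up phase without splitting by arm, and Primary outcomes has both groups assessed at weeks 2, 4 and 6. The follow-up sentence most naturally marks where the second phase starts, and the intention-to-treat statement points the same way. What remains is an ambiguity.
- *The 15% opt-out allowance shows how many would be lost.* That allowance belongs to the QLQ-C30 sample size and covers all patients. It is not a rate of treatment non-completion and cannot be applied to one arm.

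**Conclusion.** The definition is wrong for the name it carries. As written, the endpoint is time to recurrence, and it cannot support the survival conclusion that the Introduction and Discussion look forward to. This rests on the stated event list alone and needs no assumption.

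The size is uncertain. About 3 to 11 uncounted deaths among about 26 to 55 events by year 3 is an illustration that depends on a survival rate used as a proxy and on an assumed share of deaths without relapse. With so few events, a loss towards the upper end would matter to a DFS comparison. Its direction between arms cannot be known from the document.

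The follow-up wording is a secondary ambiguity between Secondary outcomes, Table 3 and Statistical analysis. Overall the point should be corrected, but it does not endanger the trial's primary analysis.

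**What to change.** Choose one of two definitions and use it throughout the Abstract, Introduction, Secondary outcomes and Discussion:

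1. Define DFS as time from randomisation to first local, regional or distant relapse or death from any cause, and report the relapse-only version separately as time to recurrence, with death as a competing event.
2. If only relapse is intended, rename the endpoint time to recurrence, state how deaths are handled, and remove the claim about survival.

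In either case, state that relapse and death are recorded with their dates from randomisation for every randomised patient, whether or not the six-week phase is completed, and state in Table 3 that the other outcome events include death.

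The cost is wording plus a dated relapse and death field at visits already scheduled. No new procedure and no change in sample size is needed. The change should be made before any outcome comparison by arm, because altering an event definition after seeing results would weaken the finding.

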#### Safety assessment

All safety parameters will be recorded in terms of listings and summary tables. We don’t expect increased risks for patients participating in the treatments given the results of earlier studies. Thus, no specific hypotheses were formulated to incorporate in the analysis.

#### Sample size

Previous studies evaluating TCM-eRhab program for early-stage CRC patients reported a mean difference of 66.1 ± 10 points after the intervention on the QOL-C30 scale. In addition, the evidence reported on the average of scores of QOL-C30 scale for CRC patients with early-stage was 61.5 ± 10 points. In order to provide 80% power to detect this clinically meaningful difference, using a two-sided test with alpha = 0.05 and assuming that 15% of patients opt out, we need to approach approximately 210 patients (TCM-eRhab intervention group:140 patients, Control group: 70 patients).

#### Data management and smartphone app

The majority of the data is collected online using app and can only be accessed by the research team. The data management process will be complied with the regulatory requirements of Clinical Trial Quality Management Regulations and Clinical Trial Data Management Work Technical Guidelines to ensure the authenticity, integrality, accuracy, and traceability of data.

We have developed an app through WeChat Platform which customized for CRC patients with psychological rehabilitation needs(software copyright registration number: 2022SR1412831). The TCM-eRhab app will be interactive and incorporate individualized professional psychology rehabilitation course, lifestyle coaching support and TCM physical activity guidance. Through the TCM-eRhab app, study data will be collection and stored on the app and access only by our team. Furthermore, TCM-eRhab program videos can also be pushed to individuals, making the user’s experience on the APP a personalized one.

### Statistical analysis

Analysis of the study will be performed using SPSS statistical software package, version SPSS26.0 (Chicago, IL, USA) by the “intention-to-treat” principle, therefor all randomized patients satisfying eligibility criteria will be included in the efficacy analysis. A comparison of demographic, social and clinical characteristics will be carried out for each arm. The primary analysis of the QLQ-C30 questionnaire and Self-reported psychological pressure scales is the domain-averaged difference in scores between TCM-eRhab intervention group and usual follow-up group after intervention. Difference in these variables between the intervention and control groups will examined using either chi-square tests or analysis of variance. To examine whether anxiety, depression and clinical syndromes are the prediction factors of metastasis after intervention, modelling will be performed in Stata.

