## Discussion

TCM-eRhab program as an online mind–body group therapy intervention has the potential to address complex constellation of symptoms. Meanwhile, TCM-eRhab program integrates treatment elements of TCM psychotherapy and modern psycho-oncology. By carrying out this randomized controlled trial, it will facilitate the development of current clinical practice towards innovative models of integrative Chinese and western rehabilitation and optimize the modern mind–body intervention methods.

The main objective of this study is to assess the evidence of TCM-eRhab program for improving CRC patient’s quality of life after radical surgery as well as benefiting their survival outcomes especially DFS. According to current ASCO guideline, promoting health condition, treating cancer related symptoms and preventing cancer recurrence are all major components of survivorship care for CRC patients. However, there is still lack of an effective and efficient intervention that could meet more patients’ needs at the same time. Thus, our study results will have profound meaning for the development an integrative intervention model of cancer survivorship care for CRC survivors.

This study will conduct online group therapy for patients which contains potentially unique therapeutic advantages such as encouraging expression, peer-support, coping skills, mindfulness practice and emotional expression. In addition, each patient will receive a comprehensive psychological, symptom and survivorship care needs assessment that is carried out at the beginning of the therapy, so that individualized TCM and supportive care plans can be integrated into the related session. So far, several studies have proved that education on lifestyle and health behavior has positive impact on CRC patients’ quality of life [20, 21]. To the best of our knowledge, the current study is one of the first to integrate methods and opinions of TCM into such education program and group therapy.

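### The programme is delivered in therapy groups, but the planned test and the sample size treat patients as independent; if outcomes correlate within groups, the standard error is too small and the 80% power may not hold

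*Protocol article*

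**What the plan says.** All references are to the protocol article.

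- **Delivery.** Interventions describes six weekly sessions of 60 to 90 minutes. Table 1 includes self-introduction and sharing of feelings. The Discussion presents interaction between patients as part of how the programme works: "This study will conduct online group therapy for patients which contains potentially unique therapeutic advantages such as encouraging expression, peer-support".
- **Control arm.** Under Usual care (Control) group, controls are not offered the programme in the first six weeks. Table 3 places every QLQ-C30 and psychological assessment at or before week 6, so only the intervention arm is grouped during the comparison.
- **Randomisation.** Patients are randomised individually, 2:1, stratified by clinical centre only.
- **Analysis.** For the between-arm comparison, Statistical analysis states: "Difference in these variables between the intervention and control groups will examined using either chi-square tests or analysis of variance". No therapy-group term is named.
- **Sample size.** The inputs are an intervention figure ("reported a mean difference of 66.1 ± 10 points after the intervention on the QOL-C30 scale"), a control figure ("for CRC patients with early-stage was 61.5 ± 10 points"), a test level ("using a two-sided test with alpha = 0.05") and attrition ("assuming that 15% of patients opt out"). The conclusion is "we need to approach approximately 210 patients (TCM-eRhab intervention group:140 patients, Control group: 70 patients". Group size, ICC and design effect do not appear.

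**The concern.** Patients who meet weekly in the same group and are meant to support one another may end up with more similar outcomes than patients in different groups. Ordinary analysis of variance and the chi-square test assume that this does not happen. If it does, the intervention-arm mean is less precise than the test supposes. The confidence interval is then too narrow, and an apparent benefit on the primary outcomes is declared too easily. Stratifying by centre does not deal with this, because therapy groups are a different level from centres.

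The same assumption underlies the sample size. The effective number of intervention patients may be smaller than the head count, so the stated power depends on a group size and an ICC that the article does not give.

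**Working it through.** **Inputs from the Sample size section.** Means 66.1 and 61.5 (reading the first as a post-intervention mean, the only reading under which the calculation works), so the difference is 4.6. SD 10, two-sided alpha 0.05, power 80%, 15% opt-out, 140 v 70.

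**Assumed, because not in the document.** Therapy-group size m (patients with outcome data) and ICC, with total SD held at 10.

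**1. The plan's own figure, under independence.**
Controls needed = (1.96 + 0.8416)² × 10² × (1 + 1/2) / 4.6² = 55.6, so 56, with 112 in the intervention arm: 168 evaluable. 168 / 0.85 = 197.6, so 198. The stated 210 is not reproduced; it is about 6% higher, on the safe side. That gap is a separate matter, but it provides the slack used in step 4.

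**2. Power of 210 under independence.**
After 15% loss: 140 × 0.85 = 119 and 70 × 0.85 = 59.5.
SE_naive = 10 × √(1/119 + 1/59.5) = 1.588.
Power = Φ(4.6/1.588 − 1.96) = Φ(0.937) = 82.6%.

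**3. Clustering in the intervention arm only.**
Design effect DE = 1 + (m − 1) × ICC.
SE_true = 10 × √(DE/119 + 1/59.5).
Power of a test that uses the correct standard error = Φ(4.6/SE_true − 1.96).
Actual level of the test that ignores groups = 2 × [1 − Φ(1.96 × SE_naive/SE_true)].

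Worked case, m = 10 and ICC 0.05: DE = 1 + 9 × 0.05 = 1.45; SE_true = 10 × √(1.45/119 + 1/59.5) = 1.703. Power = Φ(4.6/1.703 − 1.96) = Φ(0.741) = 77.1%. Level = 2 × [1 − Φ(1.96 × 1.588/1.703)] = 2 × [1 − Φ(1.828)] = 6.8%.

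| m | ICC | DE | SE_true | Power | Actual level |
|---|---|---|---|---|---|
| 6 | 0.01 | 1.05 | 1.601 | 82.0% | 5.2% |
| 8 | 0.02 | 1.14 | 1.624 | 80.8% | 5.5% |
| 10 | 0.02 | 1.18 | 1.635 | 80.3% | 5.7% |
| 10 | 0.05 | 1.45 | 1.703 | 77.1% | 6.8% |
| 10 | 0.10 | 1.90 | 1.810 | 71.9% | 8.6% |
| 15 | 0.05 | 1.70 | 1.763 | 74.2% | 7.8% |
| 15 | 0.10 | 2.40 | 1.923 | 66.7% | 10.6% |

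Rounding the control arm down to 59 changes these by 0.2 percentage points or less (the last level becomes 10.5%). A simulation of the ordinary pooled t-test (40,000 runs per scenario, 120 v 59) gave levels of 6.5%, 8.4% and 10.4% for m = 10 with ICC 0.05, m = 10 with ICC 0.10, and m = 15 with ICC 0.10. The inflation is therefore not a product of the formula.

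**4. Where 80% is lost.**
80% power needs SE_true ≤ 4.6/(1.96 + 0.8416) = 1.642. Solving, DE = 119 × (0.1642² − 1/59.5) = 1.21. The corresponding ICC is 0.21/(m − 1): about 0.042 at m = 6, 0.023 at m = 10 and 0.015 at m = 15.

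**The case against.** **Size is unknown.** The document gives no group size, number of groups or ICC, and that patients share therapists is only an inference. Group contact is six sessions. Alongside it come personalised symptom treatment, individual care plans and app content sent to individuals, all of which could dilute within-group similarity. This stands: it bars any claim about which row of the table applies. It does not show that the correlation is zero.

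**Power.** A reader might infer that the stated 80% is simply not delivered. The document's figures do not support that. 210 exceeds the 198 needed under independence, and at groups of 8 with ICC 0.02 power is still about 81%.

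**Level.** A reader might also infer that the error rate exceeds 5% outright. It need not. Patients are randomised individually, so if the programme affects nobody and groups and therapists make no difference, grouping after randomisation adds no correlation from treatment and the test keeps about 5%. Inflation requires real differences between groups together with a zero average effect.

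**Deferral.** The full protocol or an analysis plan may specify a better model, and an article commonly leaves random-effects detail to it. That weakens the point without removing it, because the article itself names the tests and all the sample-size inputs, and both rest on independence.

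**Conclusion.** The concern holds in conditional form. The stated analysis and sample size assume independence, while the stated delivery is in groups in one arm only. If outcomes correlate within therapy groups, the standard error is too small: by a factor of about 1.02 at groups of 8 with ICC 0.02 and 1.21 at groups of 15 with ICC 0.10. Power is below 80% only once the intervention-arm design effect exceeds about 1.21; below that the stated 80% holds.

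These sizes rest on assumed group sizes and ICCs and range from negligible to material. The ordinary test is not less likely to reject when groups are ignored; the power figures above are for a test with the correct standard error. Nothing here shows bias in the estimated difference itself. The point should be fixed before analysis, but it does not invalidate the design.

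**What to change.** 1. Record a therapy-group identifier for every intervention patient. The Discussion already plans to record participation in each session, so this is one more field. If it is not captured, the analysis may not be correctable later.
2. Replace ordinary analysis of variance for QLQ-C30 and the psychological scales with a partially nested linear mixed model: a random therapy-group effect in the intervention arm only, controls as singletons, and small-sample degrees of freedom.
3. In Sample size, state the planned group size and an assumed ICC, and give power conditional on them (for example, about 77% at groups of 10 and ICC 0.05) in place of the unqualified "In order to provide 80% power to detect this clinically meaningful difference".

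**Cost.** Revised analysis wording, one data field, slightly wider intervals and possibly a less favourable power figure. No additional enrolment is proposed.

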### Randomization and allocation

Following baseline assessment and registration, patients will be randomized in a 2: 1 ratio to either the TCM-eRhab program or to the normal usual care control group, using a computer-generated randomization list. Randomization will be overseen by research assistant, who will have no direct involvement in implementing the trial. Randomization is stratified by clinical center.

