### Interventions

#### TCM-eRhab intervention group

The treatment will be jointly conducted by the department of psychology rehabilitation at Beijing Cancer Hospital, TCM-psychology department at Clinical Basic Research Institute of CACMS and TCM-oncology department at Xiyuan hospital. The feasibility of this protocol has been established by our previous trial, which will last for 6 consecutive weeks, once a week, lasting 60 min to 90 min each. The intervention protocol will be divided into six subjects, namely (1): Nice to meet you. (2): How to manage our symptoms? (3): How to manage our emotions? (4): How to be friend with our body? (5): How to support out family and loved ones? (6): How to plan out future and farewell! The content of TCM-eRhab in each week is detailed in Table 1. Then, the physical symptoms of patients will be personalized treatment by the TCM-oncologist and psychology therapist. The physical symptoms management of TCM and western medicine intervention in Table 2.

**Table 1 Tab1:** Session structure of TCM-eRhab program

**Period**		**Subjects**	**Intervention instructions**	**Technics**
**Week 1**	**Initial Phase**	*Session1:* Nice to meet you	Self-introduction; What is the aim rehabilitation in TCM concept (harmony); Mindfulness practice; guide patients to care themselves and share their feelings	Expression support
**Week 2**		*Session2:* How to manage our symptoms?	How to modify lifestyle after CRC diagnosis? How to use TCM to preserve life? Why we experience symptoms and how could we use TCM to manage them?	Cognitive Training;
**Week 3**	**Work Phase**	*Session3:* How to manage our emotions?	Do you fear of cancer recurrence? How could we manage emotion and stresses? Concentration practice. Acupoints and acupressure	Expression support
**Week 4**		*Session4:* How to be friend with our body?	Can you communicate with your body? Organ scan and mindfulness practice	Cognitive Training
**Week 5**	**Final Phase**	*Session5:* How to support out family and loved ones?	Anything changed on your family and social support after cancer diagnosis? Five most important things in your life. Relax practice	Cognitive Training
**Week 6**		*Session6:* How to plan out future and farewell!	Love mindfulness practice; future plan; lucky diary; farewell	Expression support

**Table 2 Tab2:** The physical symptoms management of TCM and western medicine intervention

Syndromes	Instrument	TCM-intervention	Western Medicine-intervention

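### With 2:1 allocation, ordinary analysis of variance leaves the standard error exposed to unequal arm SDs; a variance-robust form would remove this at almost no cost

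*Protocol article*

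**What the plan says.** The Statistical analysis section of the protocol article sets the primary contrast as the between-arm difference in scores after intervention, for the QLQ-C30 and the psychological scales. The method follows: "Difference in these variables between the intervention and control groups will examined using either chi-square tests or analysis of variance". It names no variance estimator, Welch form or robust standard error. It also does not say which outcomes go to chi-square and which to analysis of variance.

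Under Randomization and allocation, "patients will be randomized in a 2: 1 ratio to either the TCM-eRhab program or to the normal usual care control group". The Sample size section gives the arm sizes: "TCM-eRhab intervention group:140 patients, Control group: 70 patients". The same section has the only SDs in the article. Earlier work on the programme "reported a mean difference of 66.1 ± 10 points after the intervention on the QOL-C30 scale", and "the average of scores of QOL-C30 scale for CRC patients with early-stage was 61.5 ± 10 points". So the planning SD is 10 on both sides.

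Only the intervention arm receives the six weekly group sessions, together with individual management: "the physical symptoms of patients will be personalized treatment by the TCM-oncologist and psychology therapist".

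**The concern.** Pooling weights the variance estimate by arm size, so at 2:1 the larger intervention arm dominates it. The true standard error of the difference depends more on the smaller control arm. The two agree only if the arm SDs are equal. With equal arms the mismatch cancels.

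Equal SDs cannot be taken for granted. One arm gets tailored, group-delivered treatment with attendance that the Discussion expects to be a challenge; the other gets usual care. Uneven response would widen the treated SD. Compression of distress scores near the bottom of a scale would narrow it. The direction is unknown, and the article predicts neither. At stake are the coverage of the confidence intervals for the primary scores and, if the treated SD is the larger, some power.

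**Working it through.** **Inputs.** From Sample size: means 66.1 and 61.5 (the first is called a mean difference but is read here as a mean), difference 4.6, SD 10 in each arm, two-sided alpha 0.05, 80% power, 15% loss, 140 + 70. After 15% loss: 140 × 0.85 = 119 and 70 × 0.85 = 59.5, taken as 59. Assumed, not from the article: any SD pair other than 10/10.

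**Step 1: the plan's own figure.** Control n = (1.96 + 0.8416)² × 10² × (1 + 1/2) / 4.6² = 7.849 × 150 / 21.16 = 55.6, so 56 control + 112 intervention = 168, and 168/0.85 = 198. The t-based version needs 57 + 114; 57/0.85 rounds up to 68, giving 68 + 136 = 204. The stated 210 is slightly conservative. At 119 v 59 the t-test has 81.9% power.

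**Step 2: size of the mismatch.** Let s1 and s2 be the intervention and control SDs.

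- Variance that pooling estimates: P = [(118 s1² + 58 s2²)/176] × (1/119 + 1/59)
- True variance: T = s1²/119 + s2²/59
- Actual two-sided error ≈ 2 × [1 − Φ(1.96 × √(P/T))]; coverage of the nominal 95% interval is 1 minus this, whatever the true mean difference.

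Ratio 0.7 (7/10): P = 65.81 × 0.02535 = 1.668; T = 0.412 + 1.695 = 2.107; √(P/T) = 0.890; 1.96 × 0.890 = 1.744; error 8.1%, coverage 91.9%.

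Ratio 1.5 (15/10): P = 183.8 × 0.02535 = 4.660; T = 1.891 + 1.695 = 3.586; √(P/T) = 1.140; 1.96 × 1.140 = 2.234; error 2.6%, coverage 97.4%.

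At 105 v 105, P = T for any SD ratio, so the formula returns 5.0%.

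**Step 3: simulation of normal scores at 119 v 59**, power for 4.6 points:

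| SDs (int/control) | Pooled error | Welch error | Pooled 95% CI covers | Power, pooled | Power, Welch |
|---|---|---|---|---|---|
| 10/10 | 5.0% | 5.0% | 95.0% | 81.9% | 81.7% |
| 7/10 | 8.1% | 5.0% | 91.9% | 92.0% | 88.0% |
| 8/10 | 6.9% | 5.0% | 93.1% | 89.3% | 86.2% |
| 12/10 | 3.7% | 5.0% | 96.3% | 72.5% | 76.4% |
| 12/8 | 2.6% | 5.0% | 97.4% | 78.3% | 85.5% |
| 15/10 | 2.6% | 5.0% | 97.4% | 57.2% | 67.5% |

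The large-sample formula Φ(4.6/√T − 1.96 × √(P/T)), with √(P/T) set to 1 for Welch, gives 73% v 77% at 12/10 and 79% v 86% at 12/8. In the rows where the treated SD is smaller, the higher pooled power is bought with error above 5%.

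For small differences the effect is slight: 5.9% error at ratio 0.9 and 4.3% at 1.1.

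**The case against.** The case against is substantial, and most of it stands.

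- **The article's own inputs show no fault.** The only SDs are 10 and 10, and with them error is 5.0%. Nothing in the text predicts unequal SDs; the reasons given above are inference from the design.
- **The null argument.** If the programme changes nobody's score, randomisation gives both arms one distribution, and alpha holds. Inflated error needs a smaller treated SD with no shift in the mean. Floor compression, the route offered to a smaller SD, itself moves the mean, so a rejection there is not a false positive. This stands. It does not rescue the interval, which should cover at its nominal level when treatment works.
- **Pooling is inferred.** The article does not say pooled, and a full protocol or analysis plan may specify a robust form. That limits the strength of the point. Still, the article does name a method, and its ordinary form pools.
- **Not every primary outcome is clearly affected.** The SAS is described in four grades, so chi-square may be intended for it. SD 10 is given for the QLQ-C30 only, and normal scores do not model floor effects.
- **Most of the power drop is not due to pooling.** At 12/10, power falls from 81.9% to 72.5%, but Welch also falls, to 76.4%. Pooling accounts for 76.4 − 72.5 = 3.9 points; the rest is the larger SD.

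A reader might infer that the trial's false-positive rate lies anywhere between about 2.5% and 8%. The documents do not support that. Those figures only reflect assumed SD ratios of about 1.5 and 0.7; a ratio of 0.5 gives 11.1% and 2.0 gives 1.7%.

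**Conclusion.** The point holds as a cheap robustness improvement. The stated method, read in its ordinary form, combines with 2:1 allocation to make the standard error sensitive to unequal SDs. Under the article's planning values nothing is lost. If treatment alters the spread of scores, nominal 95% intervals would cover roughly 92% to 97% over assumed SD ratios of 0.7 to 1.5. Pooling itself would cost about 4 points of power at 12/10 and about 7 at 12/8 (85.5 − 78.3). These results assume normal scores, 119 v 59 analysed and SD ratios chosen for illustration. They apply to primary scores analysed as continuous, and the power figures to the QLQ-C30 only. They do not show that the planned alpha is wrong.

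**What to change.** In the Statistical analysis section, for the primary scores analysed as continuous, replace the bare reference to analysis of variance with a linear or mixed model that has arm-specific residual variances, or with heteroscedasticity-consistent (HC3) standard errors. If the comparison is to be unadjusted, use Welch's test. A model is the better choice because it can also carry baseline score and the centre stratification. State that the 95% confidence interval comes from the same model as the test.

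The cost is one sentence and one software setting, with no extra patients or procedures. The downside is about 0.2 points of power if the SDs are equal (81.9% v 81.7%). The choice should be fixed before outcome data are compared by arm, since the trial is open label and a later choice of variance form would look data-driven.
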